**Figure 1. f1:**
[figure not shown]
Study design outline.

### Standard treatment

All participants in both arms will continue to receive standard care at the NIMHANS Tobacco Cessation Clinic for the duration of the trial. Standard care will be delivered in accordance with the WHO MPOWER framework and the National Tobacco Control Program guidelines of India, and will comprise three components. First, brief motivational counselling of 5 to 10 minutes at each scheduled clinic visit, delivered by trained addiction psychiatry staff, addressing motivation to quit, identification of triggers and basic relapse prevention. Second, pharmacotherapy where clinically indicated, primarily nicotine replacement therapy in the form of nicotine gum (2 mg or 4 mg) or transdermal patch, prescribed at the discretion of the treating addiction psychiatrist according to dependence severity on the FTND. Third, referral to structured psychotherapy for participants with significant comorbid psychiatric conditions requiring additional clinical management.

Standard care will be identical in both arms and will be delivered by clinicians independent of the trial team, so that any between-group difference in outcome cannot be attributed to differential background treatment. Receipt of nicotine replacement therapy and of concurrent psychotherapy will be recorded at baseline and reported by arm.

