Figure 1 provides the study design outline. Nicotine replacement therapy type and dose will be recorded at baseline, and dosage will be adjusted based on the clinical presentation of the patient by the treating psychiatrist. Any change in nicotine replacement therapy dose, or in concurrent psychotropic or psychotherapeutic treatment, during the trial period will be recorded and logged as a protocol deviation. Baseline nicotine replacement therapy status will be compared between arms and reported together with the baseline characteristics, so that any imbalance is visible to the reader. Cumulative nicotine replacement therapy exposure will not be quantified prospectively and within-trial dose changes will not be modelled as time-varying covariates; this boundary of the design is acknowledged under Limitations.

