### Limitations

The assessment schedule of this trial spans baseline, week 4 and week 8, and the design does not extend beyond the end of the 8-week intervention. Because relapse risk is concentrated in the months following a quit attempt, and because the convention in cessation research is biochemically verified abstinence at six months or longer, the trial is positioned to support conclusions about end of treatment reduction in the number of cigarettes smoked per day and short-term point-prevalence abstinence rather than about sustained cessation. Assessment at 3, 6 and 12 months lies outside the scope and resourcing of the present efficacy trial and is planned as a separate follow-on study.

Eligibility excludes severe and unstable psychiatric illness on grounds of safety and feasibility, since the intervention includes unsupervised as-needed practice that requires reliable self-monitoring, and since active severe illness would confound both adherence and the craving and dependence outcomes. This limits generalizability, because depressive, anxiety and psychotic disorders are considerably more prevalent among people with tobacco use disorder than in the general population. Participants with stable, treated depressive or anxiety disorders on unchanged pharmacotherapy remain eligible, so the sample retains part of that comorbidity, but the findings should not be extended to people with active psychosis, bipolar disorder or a current severe depressive episode, for whom a supervised adaptation of the intervention would be required.

Two further boundaries of the design are noted. Cumulative nicotine replacement therapy exposure is not quantified prospectively and within-trial dose changes are not modelled as time-varying covariates, so residual confounding arising from variation in pharmacotherapy cannot be excluded; future trials of this kind should capture cumulative exposure prospectively. Self-practice outside supervised sessions is captured by self-report and cannot be independently verified, and is therefore treated as a secondary adherence indicator rather than as a primary measure of exposure.

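### The protocol rules out background treatment as an explanation of an arm difference, but nicotine replacement can diverge after randomisation and the only by-arm comparison promised is at baseline

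*Protocol article*

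**What the plan says.** All statements are in the current text of the protocol article.

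- **Standard treatment, the claim and its basis.** "Standard care will be identical in both arms and will be delivered by clinicians independent of the trial team", and from this the section concludes "so that any between-group difference in outcome cannot be attributed to differential background treatment".
- **Standard treatment, how NRT is given.** It is offered where indicated and "prescribed at the discretion of the treating addiction psychiatrist according to dependence severity on the FTND". Referral to structured psychotherapy is a further component for participants with significant psychiatric comorbidity.
- **Study setting, dose.** After baseline recording, "dosage will be adjusted based on the clinical presentation of the patient by the treating psychiatrist".
- **Study setting, changes.** The next sentence says that a change in NRT dose, or in other psychotropic or psychotherapeutic treatment, "during the trial period will be recorded and logged as a protocol deviation".
- **What is compared or reported by arm.** Study setting: "Baseline nicotine replacement therapy status will be compared between arms and reported together with the baseline characteristics". Standard treatment: "Receipt of nicotine replacement therapy and of concurrent psychotherapy will be recorded at baseline and reported by arm".
- **What is not done.** Study setting and Limitations both say that cumulative NRT exposure is not quantified prospectively and that dose changes within the trial are not modelled.
- **Limitations, the consequence.** "so residual confounding arising from variation in pharmacotherapy cannot be excluded".

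**The concern.** The Standard treatment section draws a conclusion about what the results will mean, and the rest of the protocol does not support it. A common care policy is not the same as equal treatment received. If NRT responds to how a participant is doing, and the intervention affects how the participant is doing, then NRT can come to differ between arms because of the arm.

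At stake is the reading of the primary result. The arm difference in cigarettes per day would be the effect of Y-BLISS together with whatever changes in NRT or other co-treatment follow from allocation. A report that repeated the claim would tell readers that this component is zero, when the protocol has neither arranged for that nor committed to showing the data that would let readers judge it.

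A second problem lies in how changes are classed. The protocol provides for dose adjustment as part of care and also treats any dose change as a departure from protocol. As written, the number of recorded deviations would depend partly on participants' clinical course.

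**Working it through.** No stated figure bears on this point, so the check is a comparison of the text, followed by a short illustration on assumed inputs.

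1. **Claim against concession.** Standard treatment says a difference *cannot* be put down to background treatment. Limitations says an influence of varying pharmacotherapy *cannot* be excluded. Both cannot stand. Limitations agrees with the design described elsewhere, so the categorical clause is the one to change.

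2. **Does the premise give the conclusion?** The premise is identical care from independent clinicians; Study setting adds that treating clinicians are blind to allocation. Two features break the inference:
   - NRT is tied to FTND severity. FTND is also a secondary outcome that Y-BLISS is hypothesised to lower. It is measured at baseline, week 4 and week 8 (Table 1), and its description says it covers quantity smoked. The protocol does not say whether only the baseline score guides prescribing. If later scores do, a prescribing criterion is itself expected to differ by arm under the trial's own hypothesis.
   - Dose is adjusted to clinical presentation. This path stays open even if only baseline FTND is used. It needs no knowledge of allocation, so clinician blinding does not close it.

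3. **Is the check made at the right time?** The comparison promised is of baseline NRT status and baseline psychotherapy. Randomisation already protects baseline up to chance. The risk in step 2 arises afterwards, and a baseline table cannot show it. The within-trial changes are recorded, so the data for a later comparison will exist; the article does not commit to presenting them by arm.

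4. **Adjustment against deviation.** In Study setting, one sentence says dosage will be adjusted and the next classes any dose change during the trial as a deviation. If adjustment were confined to baseline or before, the conflict would vanish, but the text does not confine it. Psychotherapy is a narrower case: a referral already in place at baseline is not a change, but a new mid-trial referral made under Standard treatment would also be a deviation under Study setting.

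5. **Size.** The documents give no rate of NRT use, of dose change, or of effect of NRT on cigarettes per day, so the size cannot be computed from them. Purely as an illustration on **assumed** inputs, take contribution to the arm difference (in SD) = difference in NRT use between arms × effect of NRT in SD:
   - low end: 0.05 × 0.2 = 0.01 SD; 0.01 / 0.59 ≈ 2% of the planning effect size of 0.59;
   - high end: 0.30 × 0.5 = 0.15 SD; 0.15 / 0.59 ≈ 25%.

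   The range shows only that the component could be negligible or material. The direction is not fixed either. If more smoking leads to more NRT and Y-BLISS works, the control arm would get more NRT and the observed difference would tend to shrink. The protocol does not say how presentation drives the adjustment, so the opposite cannot be ruled out.

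**The case against.** The case on the other side is substantial.

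- **The limit is disclosed.** Study setting and Limitations both say that exposure is not quantified and changes are not modelled. This stands: the fault is one overstated clause, not concealment. Disclosure in one section does not cure a contrary statement in another.
- **Blinding and independence of clinicians.** These are real safeguards against arm-driven prescribing, and they would support a narrower statement that care policy does not differ by arm. They do not cover changes that follow from the participant's response.
- **Intent-to-treat is already planned.** Data analysis commits to analysing all randomised participants, and dose changes are not modelled. In substance the effect is therefore already estimated regardless of such changes. This stands. No new analysis is needed, and which label is used for post-randomisation changes is a secondary matter.

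A reader might infer more than the documents support:

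- *That the planned tables would hide NRT changes.* The article gives no list of results tables and does not say that only baseline use will be reported. What can be said is that baseline is the only by-arm comparison it commits to.
- *That an analysis set excluding deviators would be biased.* No such set is defined. The one subset, completers in Adherence monitoring, depends on attending at least 20 of 40 sessions and completing the week 8 assessment.
- *That dose changes are properly ordinary co-treatment and should not be called deviations.* The text supports either side of its own conflict. Which statement governs is a clinical-management decision for the trial team.

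**Conclusion.** The point holds as an overstated claim plus an internal conflict. The protocol asserts that background treatment is excluded as an explanation of an arm difference. Its own provisions for discretionary, individually adjusted NRT do not secure this, and its Limitations section says otherwise. The promised baseline comparison cannot reveal differences that arise after randomisation. Separately, the statements on dose adjustment and on deviations must be reconciled, with the same conflict for a new psychotherapy referral during the trial.

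The intent-to-treat comparison remains valid as the effect of allocation, including any change in co-treatment that follows from it. No sample size or primary estimate changes. What changes is what the trial may conclude about the source of a difference, and whether a reader can check it. The size is unknown; the 0.01 to 0.15 SD range rests wholly on assumed inputs. The conclusion assumes that dose adjustment can occur after randomisation, which the text does not restrict and which its references to within-trial dose changes imply. The correction should be made before results are reported.

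**What to change.** 1. In Standard treatment, delete the clause on attribution, or soften it so that it agrees with Limitations, for example by saying that the care policy and the independence of clinicians do not differ by arm but treatment received may.
2. From the changes already recorded, tabulate by arm, through week 4 and through week 8, the number of participants with any recorded change in NRT and the number with any recorded change in other psychotropic or psychotherapeutic treatment. Keep this descriptive. Adjusting for dose as a time-varying covariate would not repair the claim, since such changes may be consequences of allocation.
3. State that the intent-to-treat effect on cigarettes per day is interpreted as including any such changes.
4. Reconcile the adjustment and deviation statements in Study setting with each other, and with the psychotherapy referral component in Standard treatment. The trial team should decide which governs.

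The cost is a few sentences and one descriptive table from data the protocol already collects.

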### Selection of participants

**
*Inclusion criteria*
**

The following criteria shall be used to include the subjects for the study
a)Volunteers above 18–55 years of ageb)All genderc)No exposure to a structured yoga program of 60 minutes or more per month in the preceding 6 monthsd)Those with FTND scores above 3

**
*Exclusion criteria*
**

The following criteria shall be taken into consideration to exclude subjects
a)Those who underwent any recent surgery in the past 6 months.b)Those with very low level of dependence (FTND of 3 or below)c)Currently enrolled in a structured CBT or Quit-Smoking programd)Two or more sessions of yoga in the last one month.e)Medical conditions that might make participation of Yoga difficult or potentially hazardous (e.g., heart failure, ischemia, and hypertension).f
)Subjects with neurodegenerative disorders and neurological disorders like stroke.g)Severe or unstable psychiatric illness likely to interfere with protocol participation or to confound craving and dependence outcomes, specifically schizophrenia, bipolar disorder, or a current moderate to severe depressive episode; cognitive impairment sufficient to prevent comprehension of intervention instructions; severe hearing or visual impairment. Participants with stable, treated depressive or anxiety disorders, on unchanged pharmacotherapy for at least 3 months, are eligible.h)Pregnant womeni)Those with co-morbid dependence on other substances except alcohol.j)Those with severe alcohol dependence or in those in the state of complicated withdrawal.

### Data storage, handling, and statistical analysis

A data monitoring committee (DMC) will be created, which will be chaired by the biostatistician. The DMC will be independent from the sponsor and any competing interests. Data handling, coding and password-protected data storage will be supervised by a biostatistician. The biostatistician will also supervise data anonymization and data analysis. The data will be suitably anonymized so that no identification features are revealed. Data anonymization will be done by the biostatistician creating a mirror image of a database and implementing alteration strategies, such as character shuffling or encryption.

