### Study setting

Participants with at least mild severity of tobacco use disorder (dependence on cigarette smoking with FTND scores above 3) availing the outpatient/inpatient clinical services under the Centre for Addiction Medicine, Department of Psychiatry, and Department of Integrative Medicine, National Institute of Mental Health and Neurosciences (NIMHANS), Bengaluru, India will be approached. Participants will also be screened in the NIMHANS Centre for Well-being and online social media platforms (through an advertisement of the research project). The course of the trial, its benefits, possible demerits, voluntary participation with a choice to quit the study at any time will be explained in simple comprehensible language. Patients satisfying the inclusion criteria will be requested to provide written informed consent. Consecutive consenting patients will be randomly assigned to one of the two groups – Standard treatment + Yoga-breath linked intervention to stop smoking (Y-BLISS arm), or Standard treatment + Desktop Exercises (D-exercise arm) alone by the biostatistician. Allocation sequence will be generated by biostatistician using computer-generated random numbers and allocation concealment will be done using opaque sealed envelopes. A validated and standardized Y-BLISS program will be used as an intervention. Although double blinding will not be possible in the study, the clinicians treating the subjects, the outcome assessors, and data analysts will remain blind to the subject-group allocation status throughout the period of the study. All participants will be continuing their routine standard care (Nicotine replacement therapy and psycho-social support) till the study concludes.

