### Plans for data management, sharing and dissemination of research findings

All information pertaining to the participants would be kept confidential under the researchers. For conducting the study, each participant would be number coded instead of their name which would be only available to the researchers. Barring the Principal investigator and the study coordinator, none will have access to the final trial dataset.

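### One biostatistician role holds the allocation, supervises the analysis and chairs the DMC, which puts the stated analyst blinding at risk and makes the chair an auditor of their own work

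*Protocol article*

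**What the plan says.** All statements are in the protocol article.

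- **Allocation (Study setting).** Participants are randomised to the yoga arm "or Standard treatment + Desktop Exercises (D-exercise arm) alone by the biostatistician". The list comes from the same role: "Allocation sequence will be generated by biostatistician using computer-generated random numbers and allocation concealment will be done using opaque sealed envelopes".
- **Blinding (Study setting, repeated in the Abstract).** Along with treating clinicians and outcome assessors, "data analysts will remain blind to the subject-group allocation status throughout the period of the study".
- **Monitoring (Data storage, handling, and statistical analysis).** "A data monitoring committee (DMC) will be created, which will be chaired by the biostatistician". The next sentence reads: "The DMC will be independent from the sponsor and any competing interests".
- **Data and analysis (same section).** A biostatistician oversees data handling, coding and storage. Then: "The biostatistician will also supervise data anonymization and data analysis".
- **Discretionary decisions (Data analysis).** Missing data, drop-outs, non-compliance and adverse events are handled jointly with the biostatistician and the supervisor.
- **DMC powers (Data analysis).** The committee sees interim results and can end the trial for unreasonable morbidity or mortality. It suggests changes to design or sample size, which also need the funder's approval. It audits conduct yearly, in a process described as independent of investigators and sponsor.
- **Dataset access (Plans for data management, sharing and dissemination of research findings).** "Barring the Principal investigator and the study coordinator, none will have access to the final trial dataset".

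**The concern.** Two safeguards that the article claims depend on people being kept apart, and the article places them together. Analyst blinding is meant to keep knowledge of allocation away from choices made in the analysis. An independent DMC is meant to give a view of conduct and interim data from someone who did not produce them. A role that holds the list, supervises the data and the analysis, and leads the monitoring committee weakens both.

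The setting gives this some weight. The primary outcome is cigarettes per day, with weekly values self-reported by SMS (Clinical assessment). Sample size estimation expects 30% attrition. Interim information may also feed back into the design. If choices about incomplete or non-compliant participants involve someone who knows the arms and has seen interim results, a reader cannot rule out that this knowledge shaped them. The trial report would then carry statements on blinding and independence that the described structure does not secure.

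**Working it through.** The article gives no figure for this point, so the check traces each function to its holder.

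1. **Generating the sequence and assigning participants:** the biostatistician (Study setting). Opaque envelopes conceal the next allocation from those enrolling. They do not conceal the list from the person who made it, so this role knows the allocation.
2. **Supervising data handling and analysis:** the biostatistician (Data storage, handling, and statistical analysis). The word *also* in "The biostatistician will also supervise data anonymization and data analysis" adds this to the role's other tasks.
3. **Missing data and non-compliance:** the biostatistician together with the supervisor (Data analysis).
4. **Interim review, suggested design changes and yearly audit:** the DMC, chaired by the biostatistician.

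Now set these against the two claims.

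- **Analyst blinding.** Items 1 and 2 together give an analysis supervisor who knows the allocation. Item 4 adds access to interim results. The article does not say whether these are shown by arm, but a chair who holds the list and supervises the data could link them. The planned anonymisation removes identifying features; it is not described as masking the arm, and the same role supervises it.
- **DMC independence.** An audit of trial conduct would naturally cover randomisation, data handling and the management of incomplete data. Items 1 to 3 are therefore the chair's own work, wholly or in part. That is self-audit, whatever the chair's relation to the sponsor.

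No other statistician, coded-arm analysis or barrier between these tasks appears in the article.

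**Scale.** Expected attrition can be counted from Sample size estimation:

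- 0.30 × 144 = 43.2, about 43 participants;
- by difference from the analysable target, 144 − 100 = 44.

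So about 43 to 44 participants may have incomplete follow-up. This measures attrition, not bias. A likelihood-based mixed model can use incomplete records without a separate decision on each one.

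**Dataset access.** Study setting provides for blinded data analysts, and the data section provides for a biostatistician supervising the analysis. The dissemination section limits the final dataset to the principal investigator and study coordinator. Read literally, neither the analysts nor their supervisor could use it. This is a secondary inconsistency of wording and the main point does not rest on it.

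**The case against.** Several counter-arguments have force.

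- **The article never says that one person holds every role.** True. Study setting once uses the word without an article, and the data section once says *a* biostatistician. Still, a single role title is used throughout and no second person is introduced. One person is the natural reading; if there are two, the article needs to say which of them is unblinded and which chairs the committee.
- **Supervising is not analysing.** This stands. A separate hands-on analyst could remain blind. A reader might infer that the claim of analyst blinding is false, but the text shows only that it is at risk through the supervisor.
- **Independence is claimed only from sponsor, competing interests and, for the audit, investigators.** The biostatistician is not called any of these, so a flat textual contradiction is arguable. The self-audit remains, and a stake in one's own work can fairly be called a competing interest.
- **Discretion is limited.** This stands in part. All randomised participants are analysed by intention to treat with a mixed model. The completer definition is fixed in advance (Adherence monitoring: 20 of 40 sessions plus the week 8 assessment). Missing-data decisions are shared with the supervisor, design changes need funder approval, and a chair is one member of a committee. A reader might infer that one unblinded person decides alone; the documents do not support that.
- **Outcome collection is protected.** Assessors and clinicians are separately blinded and allocation is concealed in envelopes. The concern is with analysis and oversight, not with measurement at visits.
- **The access sentence concerns confidentiality.** That is a reasonable reading, so it is a matter of wording to reconcile. It does not show that the analysis could not be run.

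The point does not depend on detail left to an unseen analysis plan or DMC charter: the article itself makes the biostatistician the chair and the analysis supervisor.

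**Conclusion.** The concern holds in a limited form. At least four functions (allocation, analysis supervision, interim review and conduct audit) sit in one named role, which also shares the missing-data and non-compliance decisions. The supervisor of the analysis is therefore not blind, and the DMC chair would audit their own work. This puts the stated analyst blinding at risk and undercuts the stated independence.

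The conclusion assumes that the single role title means one person, and that the absence of a described barrier means none is planned. The size of any bias cannot be derived from the document. The 43 to 44 participants expected to be lost show where discretion could arise and should not be read as the number affected. It is worth settling before any interim look, because role separation cannot be restored once the results have been seen.

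**What to change.** 1. Have a DMC member with no role in randomisation, data handling or analysis take the chair.
2. State which role is unblinded. Whoever holds the allocation list or sees interim results by arm should not supervise the final analysis or take part in missing-data and deviation decisions. Moving the biostatistician from chair to the DMC's reporting statistician would not be enough if that person still supervised the final analysis, since interim knowledge would come with them.
3. Run the final analysis on arms coded A and B, with missing-data and deviation decisions signed off before unmasking.
4. Reconcile the dataset-access sentence with Study setting and with the data section, so that the blinded analyst has access to the final dataset.

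The cost is a different DMC chair, some reassignment of existing roles and the matching wording in the protocol. Sample size, visits and trial procedures are unchanged.
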